## **8.7 Premature termination of the study**

Unexpected serious side effects may be a reason to stop the study. Administration of Potassium Iodide tablets will then be discontinued immediately.

## **9. SAFETY REPORTING**

### **9.1 Temporary halt for reasons of subject safety**

In accordance with section 10, subsection 4, of the WMO, the sponsor will suspend the study if there is sufficient reason to believe that continuation of the study will jeopardize the health or safety of subjects. The sponsor will notify the accredited METC without undue delay of a temporary halt, including the reason for such action. The study will be suspended pending a further positive decision by the accredited METC. The investigator will ensure that all subjects are kept informed.

### **9.2 AEs, SAEs and SUSARs**

#### **9.2.1 Adverse events (AEs)**

Adverse events are defined as any undesirable experience occurring to a subject during the study, whether or not considered related to the investigational product, trial procedure, or experimental intervention. All adverse events reported spontaneously by the subject or observed by the investigator or their staff will be recorded. This information will be stored in the subject's electronic patient record (EPR).

#### **9.2.2 Serious adverse events (SAEs)**

A serious adverse event is any untoward medical occurrence or effect that:

- results in death;
- is life-threatening (at the time of the event);
- requires hospitalization or prolongation of existing hospitalization;
- results in persistent or significant disability or incapacity;
- is a congenital anomaly or birth defect; or
- any other important medical event that did not result in any of the outcomes listed above due to medical or surgical intervention but could have been based on appropriate judgment by the investigator.

An elective hospital admission will not be considered a serious adverse event.

The investigator will report all SAEs to the sponsor without undue delay after obtaining knowledge of the events, except for the following SAEs: not applicable.

The sponsor will report the SAEs through the web portal ToetsingOnline to the accredited METC that approved the protocol, within 7 days of first knowledge for SAEs that result in death or are life-threatening, followed by a maximum of 8 days to complete the initial preliminary report. All other SAEs will be reported within a maximum of 15 days after the sponsor has first knowledge of the serious adverse events.

### **9.2.3 Suspected unexpected serious adverse reactions (SUSARs)**

In addition to the expedited reporting of SUSARs, the sponsor will submit, once a year throughout the clinical trial, a safety report to the accredited METC, competent authority, and competent authorities of the concerned Member States.

This safety report consists of:

- a list of all suspected (unexpected or expected) serious adverse reactions, along with an aggregated summary table of all reported serious adverse reactions, ordered by organ system, per study;
- a report concerning the safety of the subjects, consisting of a complete safety analysis and an evaluation of the balance between the efficacy and the harmfulness of the medicine under investigation.

### **9.3 Annual safety report**

See above under SUSARs.

### **9.4 Follow-up of adverse events**

All AEs will be followed until they have abated or until a stable situation has been reached. Depending on the event, follow-up may require additional tests or medical procedures as indicated, and/or referral to the general physician or a medical specialist.

SAEs need to be reported until the end of the study within the Netherlands, as defined in the protocol.

### **9.5 Data Safety Monitoring Board (DSMB) / Safety Committee**

Not applicable

## **10. STATISTICAL ANALYSIS**

The primary analysis of the endpoint “clinically relevant deterioration” is a Kaplan-Meier survival analysis with the duration being the number of days since study start. Study start is the calendar day on which the first dose of Potassium Iodide tablet is administered. The difference in transfer from general ward to ICU, death on general ward, or death in ICU will be tested using a log-rank test. Hazard ratios with 95% confidence intervals will also be calculated using Cox regression analysis.

Secondary analysis will be performed for death alone and total number of days of hospital admission. For this, a Kaplan-Meier with log-rank test and Cox regression analysis will be performed.

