## SUMMARY

**Rationale:** Iodine has germicidal properties and contributes to the defense mechanism against pathogens. In addition, iodine has anti-inflammatory and immune-modulating properties that may have a beneficial effect in the treatment of COVID-19 infections. This leads to our hypothesis that iodine is effective in the treatment of COVID-19 disease.

**Objective:** To demonstrate that iodine treatment has a beneficial effect on the course of COVID-19 disease. Beneficial effect is defined as a reduced risk of deterioration, such as transfer from a regular ward to the ICU, death in the regular ward, or death in the ICU.

**Study design:** Open-label randomized trial with a control group.

**Study population:** All patients aged 18 years and older who are admitted to the hospital and test positive for SARS-CoV-2 infection will be recruited for the study. Patients must be mentally competent and able to read the patient information sheet and sign the informed consent form.

**Intervention:** Patients in the intervention group will receive, for 8 consecutive days, once daily, ¼ Potassium Iodide 65 mg tablet. The control group will receive no supplement and no placebo.

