### **3. STUDY DESIGN**

Open-label randomized clinical trial with control group.

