### **4.4 Sample size calculation**

If a less optimistic scenario is assumed, with 25% deterioration (transfer to ICU or death on ward or in ICU) in the control arm and 10% in the intervention group, the power calculation is as follows: 25% vs 10% → 100 subjects per group → 200 subjects total → 10% dropout → 224 subjects needed. An interim analysis is planned with stopping rule according to O'Brien Fleming, for which no adjustment of the sample size is needed. After 50 patients in each arm

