# **8. METHODS**

## **8.1 Study parameters/endpoints**

### **8.1.1 Main study parameter/endpoint**

Primary endpoint: clinically relevant deterioration. Deterioration is defined as:

- From baseline on general ward to ICU
- From baseline on general ward and death
- From baseline in ICU and death

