### **8.1.2 Secondary study parameters/endpoints (if applicable)**

Secondary endpoint:

- Total number of deaths
- Total number of days of hospital admission

If the subject has been admitted to the intensive care unit for part of a calendar day, this day counts as one full day of ICU admission. If the subject has been admitted partly to the ICU and partly to a general ward on a calendar day, this day counts as one full day of ICU admission. If the patient has been admitted to a general ward for part of a calendar day and has died or been discharged on that day, this day counts as one full day of general ward admission.

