## **8.2 Randomisation, blinding and treatment allocation**

Randomisation via Research Manager

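### Time zero for the primary analysis is the day of the first potassium iodide dose, so it is undefined for every control patient and for intervention patients who are never dosed

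*Protocol*

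**What the plan says.** Protocol section 10 specifies the primary analysis of clinically relevant deterioration as a "Kaplan-Meier survival analysis with the duration being the number of days since study start", tested by log-rank, with Cox hazard ratios. The definition of the clock follows at once: "Study start is the calendar day on which the first dose of Potassium Iodide tablet is administered". The sentence makes no distinction between arms.

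Other sections bear on it:

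- Summary, Intervention: "The control group will receive no supplement and no placebo".
- Section 3: "Open-label randomized clinical trial with control group".
- Section 8.1.1: the first component of the endpoint is "From baseline on general ward to ICU". The other two are death from a ward baseline and death from an ICU baseline. The moment at which baseline is taken is not stated.
- Section 8.2: the whole text is "Randomisation via Research Manager". It sets no interval between randomisation and first dose, and no section uses the randomisation date as a time origin.

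**The concern.** In a randomised comparison of survival times, both arms need the same origin, and it should be one that every randomised patient has. Here the origin is an event that only one arm can experience, and that some patients in that arm may never reach. Controls have no study start as defined, so whoever runs the analysis must invent one.

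The natural substitute is randomisation. If dosing then follows later in some intervention patients, three things can happen in that arm alone:

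- A death or ICU transfer between randomisation and first dose has a negative or undefined time and may be left out.
- Because baseline is not dated, such a transfer might be read as a patient whose baseline was in the ICU, for whom only death counts as an event.
- A patient who deteriorates and is never dosed has no clock at all.

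Each of these would remove early events from the iodine arm and keep the matching ones among controls. With open-label treatment, the choice of origin would also be made by people who can know the allocation. The interim efficacy rule in section 10.4 (p < 0.0054) and the secondary survival analyses in section 10 presumably use the same clock.

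**Working it through.** **Step 1. Can the rule be applied?** The protocol's clock needs a first-dose date.

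| Patient | First-dose date | Time zero under section 10 |
|---|---|---|
| Intervention, dosed | yes | defined |
| Intervention, never dosed | no | undefined |
| Control | no (no supplement, no placebo) | undefined |

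No section gives controls a matched start day, requires dosing on the day of randomisation, or says how to count events before dosing. The defect is thus established from the text alone. The arithmetic below only gauges what it could cost.

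**Step 2. Check the inputs against the plan's own figure.** Section 4.4 assumes deterioration "with 25% deterioration (transfer to ICU or death on ward or in ICU) in the control arm and 10% in the intervention group", and states 100 per group and 224 in total after 10% dropout. Alpha and power are not stated. Two-sided 0.05 and 80% power reproduce it:

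n = [1.96·√(2·0.175·0.825) + 0.8416·√(0.25·0.75 + 0.10·0.90)]² / 0.15² = (1.053 + 0.443)² / 0.0225 ≈ 99.5, so 100 per group. Then 100/0.90 = 111.1, rounded up to 112 per arm, or 224 in total.

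**Step 3. Illustration with no true effect.** From the protocol: 25% risk (applied to both arms) and 100 per arm. Assumed, because the protocol is silent:

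- Controls are timed from randomisation.
- Events before the first dose are lost in the intervention arm.
- The hazard decays as exp(−t/m), with m = 4 days (a mean event time of about 4 days), and with 3 and 7 days as the range.

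The total cumulative hazard is −ln(0.75) = 0.2877. Starting the clock d days late leaves the fraction exp(−d/m) of it, so the apparent hazard ratio is exp(−d/m). With d = 1:

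| m (days) | Apparent HR | Apparent intervention risk, 1 − exp(−0.2877·HR) |
|---|---|---|
| 3 | 0.72 | 18.6% |
| 4 | 0.78 | 20.1% |
| 7 | 0.87 | 22.1% |

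If only a share s of patients is dosed a day late, the apparent risk at m = 4 is about s·20.1% + (1 − s)·25%. The chance of a false result favouring iodine is approximately Φ[(Δ − 1.96·SE₀)/SE₁], where Δ is the apparent risk difference and SE₀ and SE₁ are the pooled and unpooled standard errors. For s = 1: Δ = 0.0493, SE₀ = 0.0591, SE₁ = 0.0590, giving Φ(−1.13) ≈ 13%.

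| Share dosed one day late (m = 4) | Apparent risk vs 25% | False benefit, approximation | False benefit, log-rank simulation (3,000 trials) |
|---|---|---|---|
| none | 25.0% | 2.5% | 2.3-2.4% |
| one in ten | 24.5% | 3.0% | not reported |
| half | 22.5% | 6.0% | 5.8-6.9% |
| all | 20.1% | 13.0% | 12.2-13.1% |

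With all patients a day late, the false-benefit rate is about 19-20% at m = 3 and 6-7% at m = 7.

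**Step 4. Cross-check without a timing model.** Let a share f of intervention-arm events fall before the first dose and be lost with the patients concerned. The apparent risk is then 0.25(1 − f)/(1 − 0.25f). For f = 10% this is 0.225/0.975 = 23.1%, and HR = ln(0.769)/ln(0.75) = 0.91.

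| f | Apparent HR | False benefit |
|---|---|---|
| 0 | 1.00 | 2.5% |
| 5% | 0.96 | 3.6% |
| 10% | 0.91 | 5.0% |
| 20% | 0.82 | 9.5% |
| 30% | 0.73 | 17.1% |

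The two approaches agree in order of magnitude.

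**The case against.** The best defence is that the protocol does not impose a biased comparison; it leaves the control origin open. An analysis plan could give controls a matched first study day, and if nearly all patients are dosed on the day they are randomised, a clock in whole calendar days would hardly shift. That is correct as to direction and size. It does not rescue the sentence: the protocol does not leave the origin to a later document but fixes one that does not work in one arm, and a plan that substitutes randomisation would depart from it.

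Several stronger readings are tempting and are not supported:

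- *The arms are given different time zeros.* The control origin is undefined, not stated to differ. Different origins follow only once someone picks one.
- *The primary analysis is biased towards iodine.* That depends on controls being timed from randomisation and on dosing being later. Neither is stated.
- *A transfer before dosing becomes an ICU baseline.* Baseline is never tied to the first dose. If it means location at inclusion, the transfer still meets the endpoint and only its time value fails. The fair criticism is that baseline is undated.
- *Undosed patients are excluded.* Section 10 defines a clock, not an analysis population, and analysis sets may properly sit in a document not shown here.
- *Same-day transfers are especially exposed.* A reader might infer this from the rule for a patient who "has been admitted partly to the ICU and partly to a general ward on a calendar day". That rule stands in section 8.1.2 and counts admission days for a secondary endpoint; nothing applies it to primary events.

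**Conclusion.** Wrong as written. The only time zero in the protocol cannot be applied to any control patient or to an intervention patient who is never dosed, so the primary Kaplan-Meier, log-rank and Cox analyses cannot be run as specified. This conclusion needs no assumption.

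Bias towards iodine is a risk, not an established fact, and its size cannot be derived from the protocol. Under the assumptions in the working, the false-benefit rate lies between the nominal 2.5%, if every first dose falls on the randomisation day, and about 12-13%, if every patient is dosed a day late with a mean event time of about 4 days. The upper figure widens to 6-20% for mean event times from 7 down to 3 days. Delay of a full day in every patient is the severe end of the range, not an expected value.

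**What to change.** Replace the definition of study start in section 10 with:

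> Time zero is the calendar day of randomisation in both arms. Baseline location (ward or ICU) is the location at randomisation. All randomised patients are analysed in their allocated arm whether or not a dose was taken. A transfer or death after randomisation on that day counts as an event.

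Section 8.1.1 should refer to the same definition of baseline.

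The cost is an amendment to the wording. Randomisation runs through an electronic system, so the date should already be on record. The sample size stays at 100 per group and 224 in total. With no true effect, the expected hazard ratio returns to 1.00 and the one-sided error in favour of iodine to 2.5%. The price is slight dilution of any real effect by patients not yet dosed or never dosed.

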### **8.1.3 Other study parameters (if applicable)**

BSE, CRP, leukocytes, ferritin, oxygen saturation at admission, and temperature progression. These measurements and tests are performed as part of routine care.

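### The primary log-rank test and Cox model pool ward and ICU patients, whose qualifying events differ, with no stratification by baseline location and no severity adjustment; a modest amount of power may be given up

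*Protocol*

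**What the plan says.** Protocol section 10 names a Kaplan-Meier analysis of the composite with a log-rank test: "The difference in transfer from general ward to ICU, death on general ward, or death in ICU will be tested using a log-rank test". The effect estimate comes from Cox regression. No stratum or covariate is named for either.

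The Summary and sections 2 and 8.1.1 define the composite by starting location. Patients who start on the ward have an event if they move to the ICU or die. For those who start in the ICU the only route to an event is "From baseline in ICU and death".

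On allocation, section 8.2 says only "Randomisation via Research Manager". Section 8.1.3 lists "BSE, CRP, leukocytes, ferritin, oxygen saturation at admission, and temperature progression" as other parameters, obtained in routine care, and gives them no role in the primary analysis.

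Section 4.4 sizes the trial as a comparison of two proportions, "with 25% deterioration (transfer to ICU or death on ward or in ICU) in the control arm and 10% in the intervention group", without reference to location.

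**The concern.** Because the event definition depends on starting location, ward and ICU patients are in effect followed for different endpoints. There is little reason to expect one baseline hazard to serve both. An analysis that ignores a strong prognostic factor stays valid under randomisation. However, the pooled hazard ratio is pulled towards 1, and the log-rank and Cox tests lose some power.

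The plan has no power to spare: the sample size matches about 80%, with about 35 expected events. The pooled hazard ratio is also harder to interpret, because it mixes an effect on ICU transfer or death with an effect on death alone. With no stratum in either the allocation or the analysis, nothing guards against a chance difference in ICU share between the arms.

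**Working it through.** **Inputs from the protocol.** Control risk 25%, intervention risk 10%, 100 per group, 10% dropout (section 4.4). Log-rank and Cox, no strata or covariates named (section 10). Event defined by location (section 8.1.1).

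**Assumed, because the protocol does not give them.** Two-sided 5% level, 80% power, ICU share 5% to 30%, ICU:ward hazard ratio, prognostic strength of a covariate, constant hazards over 28 days.

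**1. The plan's own sample size.** The plan states "25% vs 10% → 100 subjects per group → 200 subjects total → 10% dropout → 224 subjects needed". With mean risk 0.175:

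n = [1.96 × √(2 × 0.175 × 0.825) + 0.842 × √(0.25 × 0.75 + 0.10 × 0.90)]² / 0.15² = 99.5, so 100 per group.

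This matches. One-sided testing at 80% power gives 79, a continuity correction 113, and 90% power 133, so a two-sided 5% level with 80% power is the natural inference. Dropout: 100/0.9 = 111.1, so 112 per arm and 224 in all, which also matches.

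**2. Events and implied effect.** Expected events: 100 × 0.25 + 100 × 0.10 = 35. Implied overall hazard ratio: ln(0.90)/ln(0.75) = 0.366.

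**3. Stratifying the log-rank test by location.** Simulation with 100 per arm, overall risks held at 25% and 10%, and 2,000 trials per cell. Power, unstratified → stratified:

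| ICU share | ICU:ward hazard ratio 1 | 2 | 4 |
|---|---|---|---|
| 5% | 81.8 → 81.0 | 82.4 → 82.4 | 82.2 → 82.8 |
| 10% | 80.2 → 79.8 | 79.5 → 79.7 | 81.1 → 84.3 |
| 20% | 82.1 → 81.6 | 81.3 → 81.5 | 81.7 → 85.4 |
| 30% | 80.0 → 79.9 | 81.0 → 81.5 | 82.4 → 84.8 |

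Each power has a Monte Carlo standard error of √(0.8 × 0.2/2000) = 0.9 points. The change runs from about -1 to +4 points. At an extreme hazard ratio of 8 it is +4 to +8. With no treatment effect, the unstratified test rejected in 4.9% to 5.0% of trials.

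**4. Adjusting the Cox model for one baseline covariate, without the stratum.** Again 25% vs 10% overall, one normally distributed covariate, 600 trials per row:

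| Log hazard ratio per SD | Power unadjusted → adjusted | Median log hazard ratio for treatment | Median standard error |
|---|---|---|---|
| 0.4 | 81.2 → 83.0 | -1.02 → -1.04 | 0.376 → 0.378 |
| 0.7 | 82.5 → 85.7 | -1.01 → -1.08 | 0.379 → 0.381 |
| 1.0 | 81.8 → 88.7 | -1.04 → -1.15 | 0.379 → 0.384 |

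The standard error does not shrink. The gain comes from the estimate moving away from zero.

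**5. Stratum and one covariate together.** A further simulation at the same risks gave about +1 to +6 points at log hazard ratio 0.7 per SD (moderate) and +5 to +9 at 1.0 (strong). When neither factor was prognostic the loss was at most about 1.5 points. The ends of these ranges shift by a few points with the assumed scenario and with Monte Carlo error, so read them as orders of size.

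**6. Chance imbalance.** With 20% in the ICU (assumed) and 112 per arm, the between-arm difference in ICU share has SD √(2 × 0.2 × 0.8/112) = 5.3 points. At a hazard ratio of 4 and this share, the simulated control risks are 17.7% on the ward and 54.2% in the ICU, a gap of 36.5 points. One SD of imbalance then moves the arm difference by about 0.053 × 36.5 = 1.9 points, against a planned difference of 15.

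**The case against.** The strongest reply is that this is silence, not error. Section 10 does not call the analyses unstratified or unadjusted, section 8.2 does not exclude strata, and covariate lists are commonly left to a statistical analysis plan, which is not at hand. Worsening from the patient's own starting state is a coherent composite, and randomisation protects the comparison.

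Much of this stands. It weakens the covariate part most. It is less persuasive for location: section 10 names the primary test itself, a stratified log-rank is a different test, and a later analysis plan cannot add a randomisation stratum for patients already enrolled.

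The reply is also right about size. Stratifying changes almost nothing if the two hazards are within a factor of 2. The requirement that patients be competent and able to read and sign (Summary, section 11.3) probably keeps the ICU share low. Chance imbalance moves the result little.

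A reader might infer three stronger things, none of which holds:

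- **That precision is wasted.** The standard error is no smaller after adjustment (0.379 against 0.384), so the confidence interval for the log hazard ratio would not narrow.
- **That power rises from 64% to 75% with a strong covariate.** That result comes from using 0.366, the hazard ratio implied by the overall risks, as if it held within covariate levels. The intervention risk then becomes about 11.6% instead of 10%, so part of the apparent loss is a smaller assumed effect.
- **That severity data exist for every patient at baseline.** Section 8.1.3 says only that the measures belong to routine care. Only oxygen saturation is tied to admission, and temperature progression is post-baseline and unsuitable as a covariate.

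**Conclusion.** The point holds as a modest gain in power and interpretability. The primary analysis pools two groups whose qualifying events differ, and it makes no use of location or of a severity measure already listed. The pooled test is not invalid, and the documents do not show a large loss.

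Stratifying by location is worth about -1 to +4 points of power for ICU:ward hazard ratios of 1 to 4. The stratum plus one covariate is worth about +1 to +6 points at moderate and +5 to +9 at high prognostic strength. All of these figures rest on assumed ICU shares, hazard ratios and prognostic strengths, with two-sided 5% testing and overall risks of 25% and 10%. The protocol supplies only the risks and the group size.

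**What to change.** In section 10, make the primary log-rank test and the Cox model stratified by location at randomisation (ward or ICU). Adjust the Cox model for at most two prespecified baseline covariates, oxygen saturation at admission and age; about 35 events will not support many more. Report the unstratified, unadjusted result as a sensitivity analysis. If enrolment allows, also set ward/ICU as a stratum in the randomisation system (section 8.2).

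The cost is a change of wording and possibly one system setting. No new measurements are needed. If neither factor is prognostic, up to about 1.5 points of power are lost. Because admission saturation is a routine-care measure, the plan must also state how a missing value is handled.

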## **8.6 Follow-up of subjects withdrawn from treatment**

Follow-up lasts as long as the patient is hospitalized.

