### **10.2 Secondary study parameter(s)**

Total number of deaths and total number of days of hospital admission.

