#### **11.4 Benefits and risks assessment, group relatedness**

The likelihood of side effects is derived from the listings in the pharmacotherapeutic compass for Potassium Iodide 65 mg tablets. The side effects listed there are relatively mild and in principle transient. In rare cases, in patients with pre-existing thyroid disorders, thyrotoxicosis may occur. Temporary medicinal treatment may then be necessary to

correct thyroid dysfunction. However, this is not expected since thyroid disorders or medication related to thyroid dysfunction are exclusion criteria. The risk of side effects at the dosage of Potassium Iodide used in this study is very limited. By applying exclusion criteria for thyroid disorders and medication related to thyroid dysfunction, the chance of thyrotoxicosis is virtually eliminated. Other side effects are relatively minor and usually transient. There are no long-term health risks expected with this short-term Potassium Iodide treatment. The potential benefits for the patient may be significant, such as a better chance of survival, faster recovery, and shorter duration of hospital admission. Furthermore, there may be less irreversible lung damage, so that the quality of life after the illness period will be better.

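### Hospital days are analysed by Kaplan-Meier, log-rank and Cox without treating death as a competing event, so an early death can count as a short stay

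*Protocol*

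**What the plan says.** Section 10.2 of the protocol gives the secondary parameters as "Total number of deaths and total number of days of hospital admission", for all patients and without restriction to survivors. Section 10 fixes the method: "Secondary analysis will be performed for death alone and total number of days of hospital admission", followed by "For this, a Kaplan-Meier with log-rank test and Cox regression analysis will be performed". It states no event, censoring rule or competing risk for hospital days.

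Section 8.1.2 has the only counting rule. It allocates part-days to ICU or general ward. For a ward patient who "has died or been discharged on that day, this day counts as one full day of general ward admission", death and discharge are handled identically. A part-day in the ICU also counts as a full day, so for a patient who dies there the count likewise stops on the day of death.

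Section 11.4 lists a better chance of survival among the possible benefits, together with "faster recovery, and shorter duration of hospital admission".

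**The concern.** Death prevents discharge, so the two are competing events. A time-to-event analysis of hospital days has to say what death does, and both ordinary answers cause trouble.

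- **Death ends the stay, as the counting rule suggests.** A patient who dies on day 3 scores the same as one who goes home on day 3. A short stay is the favourable direction, so an early death counts as a good result. A patient who is saved and then needs a long admission counts against the treatment.
- **Death is censored.** Kaplan-Meier then treats the dead as patients who would have gone on being discharged at the rate of those still in hospital.

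Death is not a rare complication here: it is a component of the primary endpoint, which is planned "with 25% deterioration (transfer to ICU or death on ward or in ICU) in the control arm and 10% in the intervention group". At stake is the reading of one of two secondary endpoints. A reader could conclude that iodine prolongs admission when it lowers mortality, or shortens it when it raises mortality.

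**Working it through.** **The plan's own figure.** The protocol gives no figure for hospital days. Its sample size reads "100 subjects per group → 200 subjects total → 10% dropout → 224 subjects needed". Alpha and power are not stated beside it. With two-sided 5% and 80% power (assumed), n = [1.96·√(2·0.175·0.825) + 0.842·√(0.25·0.75 + 0.10·0.90)]² / 0.15² = (1.053 + 0.443)² / 0.0225 ≈ 99.5, so 100 per arm. With dropout, 100/0.90 = 111.1, so 112 per arm and 224 in total. This reproduces. I use 100 per arm below.

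**Inputs that must be assumed.** The protocol gives no death rate, discharge rate or length of stay. The 25% and 10% in section 4.4 include ICU transfers, so they are upper bounds for mortality.

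**Scenario with constant rates.** Discharge q = 0.10 per day in both arms; death d = 0.02 (control) versus 0.01 (iodine) per day; 28 days. The day is my choice and is not in the protocol.

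- Discharged alive by day 28 = q/(q+d)·[1 − exp(−28(q+d))]. Control: 0.833 × 0.965 = 80.4%. Iodine: 0.909 × 0.954 = 86.7%.
- Dead by day 28 = d/(q+d)·[same bracket]. Control: 0.167 × 0.965 = 16%. Iodine: 0.091 × 0.954 = 9%.
- Death as end of stay: hazard ratio = (0.10 + 0.01)/(0.10 + 0.02) = 0.917. Medians: ln 2/0.12 = 5.8 days and ln 2/0.11 = 6.3 days. Iodine appears to keep patients in longer.
- Power of that misleading signal: about 96.5 + 95.4 = 192 stays end by day 28, so z ≈ ln(0.917)·√(192/4) ≈ −0.6. The chance of a significant result in the wrong direction is about 9%.
- Death censored: hazard ratio = 0.10/0.10 = 1.0. The Kaplan-Meier estimate of discharge by day 28 is 1 − exp(−2.8) = 93.9% in both arms. That is 13.5 points above the true 80.4% in control and 7.2 points above the true 86.7% on iodine.

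**Range under other assumptions.** Log-rank tests were simulated with 100 per arm and 300 runs per setting. Survivors stay about 8 days. The time of death and the stay of patients saved by treatment are varied. Positive z favours treatment. In brackets: for the first two analyses, the share of runs significantly against treatment; for the last, the share significantly in favour.

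| Mortality, control vs iodine | Stay of saved patients | Death at about | Death ends stay | Death censored | Discharge alive, deaths kept in risk set |
|---|---|---|---|---|---|
| 15% vs 5% | 20 days | day 4 | −1.80 (42%) | −0.99 (17%) | +1.26 (24%) |
| 15% vs 5% | 20 days | day 6 | −1.51 (36%) | −0.71 (13%) | +1.20 (23%) |
| 15% vs 5% | 20 days | day 12 | −0.73 (9%) | +0.09 (3%) | +1.37 (27%) |
| 15% vs 5% | 8 days | day 4 | −0.47 (6%) | +0.37 (1%) | +1.95 (52%) |
| 15% vs 5% | 8 days | day 6 | −0.18 (5%) | +0.59 (1%) | +1.84 (47%) |
| 15% vs 5% | 8 days | day 12 | +0.44 (2%) | +1.12 (1%) | +1.92 (52%) |
| 25% vs 10% (upper bound) | 20 days | day 4 | −2.46 (70%) | −1.29 (26%) | +1.63 (38%) |

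In the first row the mean stay is 7.9 days in control and 9.5 on treatment. With death as the end of stay, the sign changes with the timing of deaths. With discharge alive and deaths kept in the risk set, it is positive in every row.

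**The case against.** **Section 10 does not say that death is the event.** The counting rule in section 8.1.2 is about part-days, and event definitions are often left to an analysis plan, which is not at hand. This stands in part: that death ends the stay is a reading, not a stated rule. But the protocol does fix the endpoint (all days, all patients), a rule that stops the count at death, and the methods. An analysis plan could repair this only by adding a competing-event definition that the protocol does not contain.

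**A Cox model with deaths censored is valid.** It is, for the cause-specific discharge hazard. In the constant-rate scenario its hazard ratio of 1.0 is correct, because iodine does not speed discharge there. It would be too strong to say that no version of the planned analysis tells anything about recovery. What misleads is the Kaplan-Meier curve, and the hazard ratio alone does not show how many patients go home.

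**Mortality is analysed separately.** It is, and it is also part of the primary endpoint. A survival benefit would not go unseen. This limits the harm but does not make the hospital-days result interpretable.

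**Two stronger readings are not supported.** A reader might infer that a life-saving effect always appears as a longer stay; the last 15% versus 5% row shows that it need not. A reader might also take the word total to include days before randomisation. The protocol gives no starting day for this count, so nothing can be concluded from that.

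**Conclusion.** The point holds as a flaw in the stated method for one secondary endpoint. The protocol applies survival methods to hospital days without treating death as a competing event, and its only counting rule ends the stay at death and at discharge alike. On that reading the endpoint can move against a treatment that prevents death.

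The size is conditional. In the constant-rate scenario the distortion is modest: a hazard ratio of 0.92 and half a day in the median, against a true gain of about 6 points in discharge alive. With early deaths and long stays among saved patients, 36% to 42% of trials would show a significantly longer stay on treatment at 15% versus 5% mortality, and 70% at the upper bound. With short stays among saved patients it is negligible, and with late deaths as well it reverses. All these rates and times are assumptions. What does not depend on them is that the sign of the result is partly set by when patients die, so it cannot be read as shorter or longer recovery.

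**What to change.** Define the event as discharge alive, timed from randomisation in both arms to a fixed day that the sponsor names. Randomisation is the safer origin because the study start in section 10 is the day of the first dose, which control patients never receive. Treat death as a competing event: cumulative incidence curves, Gray's test and a subdistribution hazard ratio, with deaths kept in the risk set to the fixed day. Report this beside the planned analysis of death. Give raw hospital days only as description among survivors.

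This needs only in-hospital dates. The one follow-up statement, section 8.6 (written for patients withdrawn from treatment), says "Follow-up lasts as long as the patient is hospitalized", which is enough. Hospital-free days to a fixed day is not an interchangeable alternative: it needs vital status and readmissions after discharge, which the protocol does not secure, and, with death scored worst, it ranks death below still being in hospital.

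The cost is a change of wording in sections 8.1.2 and 10 and a little extra analysis. No new data are needed, and the primary endpoint and sample size stay as they are.
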